## Abstract

**Background:**

Patients who undergo surgery for cancer of the head and neck and their families face complex and difficult challenges and are at risk of anxiety and depression and inability to cope with symptom and treatment burden. Information available to support them is not flexible enough to adjust to individual need.

**Design/Methods:**

A randomised clinical trial pre and post intervention design, comparing the use of a tailored DVD intervention, provided preoperatively and used throughout the post- operative period, with usual treatment. One hundred fifty-six individuals or partner couples will be randomly recruited into either the intervention or control group. A survey will be administered at three time points, preoperatively, post operatively and 3 months post-surgery. Anxiety and empowerment are the primary outcome measures. Qualitative data about use of the resource will be gathered by phone interview.

**Discussion:**

This is the first study to rigorously evaluate the impact of a DVD intervention for this group of patients and their family members. The study will help to understand the impact of information usage on patient and family well- being and test a means by which to evaluate information and education resources for this and other cancer patient groups.

**Trial registration:**

ACTRN12614001104640. Date registered: 17/10/2014.

## Background

Head and neck cancer has a global burden of more than 550,000 cases annually [1]. Incidence rates vary between countries due to increased rates with tobacco epidemics currently peaking in some regions while declining in others where tobacco use has peaked and is falling, and with the increasing incidence associated with human papillomavirus infection [2]. Head and neck cancers diagnosed in Australia in 2009 (3896) accounted for 3.4 % of all cancers diagnosed (114,137), with the number of head and neck cancers diagnosed increasing between 1982 (2475) to 2009 (3896). This increase is attributed to an increasing aging population [3].

The treatment for head and neck cancer is often drastic and debilitating, with surgery effecting vital functions such as swallowing and breathing, as well as speech. This frequently results in poorer patient outcomes in terms of quality of life [4] that have long term impact and require significant lifestyle and psychological adjustment by patients and families [5].

Evidence points to the need for significant and broad ranging support for this group of patients who can often be overlooked in large scale cancer support programs [6]. In many cases, the complexity of the physical and functional impairments resulting from head and neck cancer or the treatment can lead to high levels of anxiety, impacting negatively on self-image, self-efficacy [7] social isolation, and depression [8]. Holland and Weiss [9] have recommended that psychosocial aspects should be integrated into routine cancer care for these patients throughout their illness trajectory. Provision of information to cancer patients has been shown to reduce anxiety and support decision making [10]. However the amount of evidence available to support information interventions is small and limited by poor quality and lack of attention to practical implementation [11].

The availability, content and quality of written information specific to the individual needs of patients with head and neck cancer have been repeatedly identified as areas requiring attention [12, 13].^,^ It is well-documented that patients require personalized information to be able to participate optimally in decision-making and self-care and that information giving needs to be informed by the preferences of patients and families and matched to significant events that occur across the illness trajectory [5].

The role of partners and family members in supporting cancer patients is also recognised as central to patient well- being [10]. They may also be impacted by the burden of care and treatment [14], and hence require timely targeted information that increases their understanding and capacity to contribute to care. Carers are also at risk of psychological distress, with reports of up to 70 % of carers of cancer patients experiencing depression and 39 % reporting anxiety [15, 16]. A recent review identified that some partners and family caregivers’ most prominent needs pertain to curtailing the impact of their roles and responsibilities on daily living and information (e.g., what to expect) [17].

A recent review of online interventions for cancer patients finds that the majority of evaluations of information related interventions focus on patient usage and satisfaction, with few reporting quantifiable clinical outcomes [18]. Additionally, there are very few studies reporting specifically on the impact on clinical outcomes. For example, [19] report on a web-based psycho-educational program for cancer patients and their caregivers that delivered a post-intervention decrease in emotional distress, and improvements in quality of life indicators. Similarly, a Korean internet-based cancer-related fatigue program, reports significant improvements in fatigue, quality of life, and anxiety for the intervention group [20]. Another program that provided head and neck cancer patients with educational resources, the ability to engage with other patients via an online forum, and an at-home monitoring system, found a significant improvement in quality of life indicators after 6 weeks compared to the control group, although this difference was not sustained after 6 months [21]. However, given the design of this study, the effect of providing educational resources alone could not be assessed. While internet-based educational programs for cancer patients certainly offer promise, variable skills in technology use have been highlighted as a confounding factor in the assessment of such intervention programs, particularly for an older cohort [18]. An Australian intervention providing prospective chemotherapy patients with a DVD preparing them for treatment and possible side effects, found benefits in improving patients’ confidence in coping with cancer, although it did not reduce pre-treatment anxiety. Nonetheless, the authors reinforce the need to provide patients with informational resources such as DVDs, as an adjunct to education provided directly by clinicians, given increasing challenges resulting from workforce shortages and the greater emphasis on ambulatory care [22].

In response to clinicians’ concerns regarding the unmet needs of patients who undergo surgery for head and neck cancers we undertook a qualitative study to identify the needs of this group of patients and their family members [5]. An important finding from this study was participant’s reports of the inadequacy of information provided to them and the difficulties they had understanding and using information effectively. Information is often developed for or by health professionals and hence may use language not easily understood by patients and their families. The needs identified included the need to feel in control and to have information about what to expect at various stages. Concerns varied according to the tumour site and the nature of surgery and any adjuvant therapies. Because of the many and varied types of surgery it was not surprising that very few people felt they had information specific to their needs [5]. These finding supports research that highlights the importance of accurate, comprehendible and timely information pre-surgery and post-surgery for head and neck cancer patients [23, 24]. At present there appears to be no systematic way for patients and partners to gain information at the various stages across the surgical journey and in accordance with their changing needs. The study described in this protocol aims to evaluate a DVD resource produced for this purpose.

## Methods/Design

### Study design

A multicentre randomised pre and post intervention design controlled trial (RCT) testing the effectiveness of a DVD information resource intervention. The overall aim of this study is to evaluate impact on mood, coping and self- efficacy, together with the utility of the first DVD education intervention designed to meet the information needs of head and neck cancer patients who undergo surgery in Australia and their partners and family members.

The primary hypothesis is: Patients and carers in the intervention group will report lower anxiety post-op and 3 months post-baseline compared to those in the control group.

The secondary hypothesis is: Patients and carers in the intervention group will report lower depression and symptom distress, fewer unmet information needs, and feel better prepared for the various steps in their treatment compared to those in the control group.

The study was funded by a Hunter New England Health District Innovation Support Grant.

### Setting

Two large metropolitan and one large regional hospital across two States in Australia. Patients recently diagnosed with a cancer of the head and neck and who are referred for surgery, and their nominated partner, carer or family member will be recruited from participating sites where surgery for Head and Neck cancers is conducted.

### Participants

Participant inclusion criteria are:Group 1. Adults aged 18 and over who have been diagnosed with a primary, early-stage head and neck cancer, whose treatment plan includes surgery.Group 2. Partners or family members aged 18 and over involved in the care and support of patient participants from Group 1.

Participants will need sufficient fluency in English and be able to participate in the study. While the aim is to recruit dyads where possible, consenting patients whose partner, carer or family member does not consent to participate, will still be eligible.

In accordance with our sample size calculation 156 (78 in in the intervention group and 78 in the control group) will be recruited into the study. If they have a partner, carer or family member who is also willing to participate they will be recruited and provide ‘linked’ data to the patient’s responses. Therefore we aim to recruit 156 individual patients or patient couples (total 156 to ≤312 individuals). The probability is 80 % that the study will detect a minimum important difference of 1.5 on HADS scores at a one-sided 0.05 significance level.. This is based on the assumption that the standard deviation of the response variable is 3.75

#### Recruitment

Clinicians will identify patients meeting the inclusion criteria during their initial specialist appointment or multidisciplinary team meeting (MDT) appointment. The surgeon or care coordinator will introduce eligible patients to the study and give interested participants a study pack, including study information and a consent form and a similar study pack to pass on to their partner, carer or family member. A Clinical Nurse Consultant (CNC) will consent the patient to the study and conduct the baseline survey at the pre-operative clinic. If the partner, carer or family member is not present, the baseline survey will be posted with a reply paid envelope to be completed at home. Following this, the CNC will apply the outcome of randomisation and the participant will be allocated to treatment as usual or the intervention group.

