#### Randomisation

A randomisation schedule will be established for each site using the website Randomization.com (http://www.randomization.com) to generate block randomised allocation to either the treatment or control using random block sizes. The schedule concealment will be maintained by a researcher at the central site who will not be involved with recruiting the patients to ensure allocation is concealed. Once participants are identified as eligible for the study, the recruiter will contact the researcher by phone or email to register the participant to the trial, including assigning the participant a unique study ID and allocating them to one of the conditions as per the randomisation schedule. Participants will not be blinded as this is a trial of a resource in addition to usual treatment, as such participants will be aware if they received the intervention DVD or not. If patients don’t complete the baseline survey, they will not be randomised to the trial. Patients will mostly use the study intervention at home, hence the chance of control participants being exposed to the intervention is minimal.

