### Data collection

Data will be collected using a self-administered survey (one for patients and one for partners, carers or family members) at three time points i.e.,; baseline (prior to surgery), post-surgery (usually at follow up clinic) and 3 months post-baseline. Information about how the resource is being used and who is using it will also be collected via phone call at T2.

Those participants randomised to the intervention group will receive the intervention DVD to take home and a follow-up phone call will be made with a week to ensure they are clear about how to use the DVD. Follow up surveys will be conducted at the post-op clinic visit and again at 3 months post-surgery. At time point 2 participants will again be contacted by phone to discuss how the resource is being used and to identify any concerns that may have arisen. A standardised discussion guide with questions regarding the DVD will be used and handwritten notes taken. The 3 month follow up may be conducted via post, telephone or web survey (Fig. 2).

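### The plan does not ensure that a posted partner baseline survey is completed before allocation is known and the shared DVD is at home

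*Protocol article*

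**What the plan says.** All references are to the Protocol article.

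- **Recruitment, patient.** The nurse "will consent the patient to the study and conduct the baseline survey at the pre-operative clinic".
- **Recruitment, absent partner.** In that case "the baseline survey will be posted with a reply paid envelope to be completed at home".
- **Recruitment, next sentence.** "Following this, the CNC will apply the outcome of randomisation and the participant will be allocated to treatment as usual or the intervention group".
- **Randomisation.** The only baseline condition concerns patients: "If patients don’t complete the baseline survey, they will not be randomised to the trial". The same section says that participants cannot be blinded.
- **Intervention.** The DVD is normally handed over at the pre-operative clinic. There is one per dyad, to be watched alone or together.
- **Data collection.** "Those participants randomised to the intervention group will receive the intervention DVD to take home". The baseline time point is defined by reference to surgery only, not to allocation or to receipt of the DVD.
- **Data analysis.** Anxiety at the three time points is analysed with a generalised linear mixed model, and the same class of model is used for secondary outcomes. Partners are secondary and lie outside the sample size calculation, although the primary hypothesis under Study design names carers as well as patients.

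**The concern.** A baseline value is useful in a randomised comparison because neither the allocation nor the treatment can have influenced it. The patient's baseline has that protection. The absent partner's does not: it travels by post, is completed without supervision, and its return is not a condition for anything that follows.

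The trial is unblinded and the outcome is self-reported (HADS). A partner who fills in the form after the patient comes home may know the arm. In the intervention arm, that partner may also have watched the DVD. The form would still meet the plan's definition of baseline as long as surgery had not yet taken place.

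What is at stake is the partner comparison. If the intervention-arm baseline has already moved, or if knowing the allocation has moved either arm, then a change from baseline or a baseline-adjusted contrast no longer estimates the full effect of the intervention. Whether the form is returned at all could then also depend on arm.

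**Working it through.** **1. Order of events for a dyad whose partner misses the clinic**

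| Step | What the plan fixes | Does it wait for the partner's form? |
|---|---|---|
| Patient baseline | At the pre-operative clinic, with the nurse | Not applicable |
| Partner baseline | Posted, completed at home, mailed back | Not applicable |
| Allocation | After the survey steps, by sentence order in Recruitment | Not stated; Randomisation makes only the patient's form a condition |
| DVD hand-over | Usually at the pre-operative clinic | Not stated; if given at that visit, a form posted because the partner is absent cannot yet be back |
| DVD at home | Shared by the dyad | Not stated |

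The Participants section also keeps a patient eligible when no partner consents, so no partner form is needed before allocation. If allocation did wait for the returned form, the DVD could not be given to these dyads at its usual place. The passages can be followed as written and still produce a partner baseline dated after allocation.

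**2. The plan's own figure**

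Inputs from Participants: difference 1.5, SD 3.75, one-sided 0.05, power 80%.

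n per arm = 2 × (1.645 + 0.842)² × (3.75 / 1.5)² = 2 × 6.18 × 6.25 ≈ 77.3, rounded up to 78, or 156 in total. This matches the plan. Power at 78 per arm is 0.803 (normal approximation) or 0.800 (noncentral t). The calculation uses patients only, so nothing here changes it. Partners number between 0 and 156 (312 − 156). The plan gives no figure for how many would be absent from the clinic.

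**3. Illustration of possible size (assumptions, not figures from the plan)**

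Suppose the true partner benefit is 1.5 points; that is the patients' planning difference, borrowed for scale. Let f be the share of intervention partners who complete baseline after exposure, and s the share of the benefit already present by then. Assume no shift in controls. The baseline contrast is then f × s × 1.5.

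- Change from baseline: 1.5 − f × s × 1.5 = 1.5 × (1 − f × s).
- Baseline as covariate, with assumed correlation 0.5 and equal SDs: 1.5 × (1 − 0.5 × f × s).
- Follow-up values only: 1.5, not affected in this way.

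| f = s | Change from baseline | Covariate-adjusted |
|---|---|---|
| 0.25 | 1.41 | 1.45 |
| 0.5 | 1.13 | 1.31 |
| 1 | 0 | 0.75 |

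The sign is not fixed. If early viewing raised anxiety, s would be negative: with f = 0.25 and s = −0.25, the change contrast becomes 1.5 × (1 + 0.0625) = 1.59. A reaction to the allocation itself could shift either arm.

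**The case against.** The strongest reply is that the plan already puts baseline first. Recruitment describes the patient's survey, then the partner's posted survey, and only then allocation, introduced by "Following this, the CNC will apply the outcome of randomisation". That stands as evidence of intent. It does not show that allocation waits for the posted form's return, and neither the patient-only condition nor the usual place of DVD hand-over suggests that it does. Figures 1 and 2 (delivery pathway and timeline) were not available for this review and might show the order more clearly.

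Second, the bias depends on the model. The article does not say whether partner analyses use change from baseline, adjustment for baseline, or follow-up contrasts alone, and the primary hypothesis compares the groups at follow-up. This stands, and it is why the point is limited to analyses in which baseline enters.

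Third, the early effect may be small. The DVD is meant for use through surgery and recovery, and the Background cites a chemotherapy-preparation DVD that did not lower anxiety before treatment. This also stands.

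A reader might infer something stronger: that absent partners' baselines are in fact post-intervention, and that the partner effect is pulled toward zero by a known amount, such as half of the 1.5-point difference. The documents do not support this. A loss of 0.75 points in a change contrast needs, for example, half of the intervention partners to be exposed and the whole benefit to be present before surgery. Neither is stated, and the direction itself is open.

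**Conclusion.** The point holds in a limited form. The protocol intends baseline first but does not secure it for partners who are absent from the pre-operative clinic. Some of their baselines may be completed after allocation is known or after the DVD has been seen, which can bias any partner analysis that refers to or adjusts for baseline.

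The size and direction cannot be determined from the documents. The figures above only show how the result depends on the assumed shares and on the model chosen. The effect is confined to absent partners, whose outcomes are secondary. The patient comparison, its baseline and its power are untouched. This is a worthwhile, inexpensive correction to a stated procedure. It is best made before recruitment, because the timing of an undated form cannot be recovered later.

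**What to change.** 1. **Collect earlier where possible.** Obtain the partner's baseline before allocation is disclosed to the dyad. It could go with the partner study pack and consent form already handed out at the first specialist or multidisciplinary appointment. It could also be taken by telephone or web once the partner has consented; both routes are already foreseen for the 3-month survey.
2. **Do not hold up the patient.** If the partner's form has not come back, randomise the patient as planned.
3. **Record dates.** Put a completion date on the partner form, and log the dates of allocation and DVD hand-over.
4. **State the analysis rule.** In the partner mixed model, treat a baseline dated after allocation as missing and keep that partner's follow-up data. A mixed model with a common baseline mean for the two arms allows this. Add a sensitivity analysis that shows the result with the late forms included.
5. **Clarify the text.** Define the partner baseline as completed before allocation is known, and reconcile Recruitment, Randomisation and Intervention on the order of steps.

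The cost is a change in when one form is handed out or how it is collected, a date field and one analysis rule. The downside is that some partner baselines will be missing, and others will be slightly earlier than the patient's, so the paired data are a little less contemporaneous.

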#### Randomisation

A randomisation schedule will be established for each site using the website Randomization.com (http://www.randomization.com) to generate block randomised allocation to either the treatment or control using random block sizes. The schedule concealment will be maintained by a researcher at the central site who will not be involved with recruiting the patients to ensure allocation is concealed. Once participants are identified as eligible for the study, the recruiter will contact the researcher by phone or email to register the participant to the trial, including assigning the participant a unique study ID and allocating them to one of the conditions as per the randomisation schedule. Participants will not be blinded as this is a trial of a resource in addition to usual treatment, as such participants will be aware if they received the intervention DVD or not. If patients don’t complete the baseline survey, they will not be randomised to the trial. Patients will mostly use the study intervention at home, hence the chance of control participants being exposed to the intervention is minimal.

### Intervention

The intervention involves a DVD for patients and their partners integrated into pre and post-surgical care. Participants will receive the education resource, in the form of a DVD, pre operatively, usually in the pre op clinic, as well as information provided as usual care. Each dyad (patient and partner) will receive one DVD which they may use individually or together.

The DVD comprises a series of chapters in which key issues and events are addressed through conversations with patients and staff (Fig. 1). The purpose of the DVD is to provide information and opportunity for patients and families to have their questions and concerns addressed as they progress from surgery through to recovery or on to adjunctive therapies. The DVD is designed in a way that participants can tailor what they learn, how often they engage with the DVD and its associated resources and how much support they seek in working with the resource.

